**Participant surveys:** A brief enrollment survey will collect patient-level data to better understand barriers experienced by patients, and assess CC knowledge, motivation to get screened, extent of partner support, mental health, risk of violence, language preferences, and education to gain a sense of literacy levels (both arms, Appendix 1). These instruments are modified from those used in HITSystem studies to assess changes that may mediate or moderate intervention impact. Women who screened positive for precancerous lesions during the study period will be asked to complete a survey including the same measures in addition to questions assessing their CC screening experience and treatment decisions within 6 months of the positive screen or at the conclusion of treatment (both arms, Appendix 2). Women diagnosed with invasive CC will be asked to engage in an interview to understand experiences accessing and receiving treatment at referral sites, the impact of the treatment process/disease on their psychological, social, physical, sexual, and financial health, and the type of support received and needed (both arms, Appendix 3). Costs associated with seeking screening and treatment will be included in these surveys. The remuneration plan for participant and provider surveys are outlined in the Human Subjects section.

**Facility assessment form:** will be completed at all sites at the beginning, mid-point and end of study implementation to assess resource level, annual CC screening volume, and CC screening provider-patient ratios to evaluate factors that contribute to implementation feasibility overtime. (See Appendix 4)

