**Provider surveys:** At baseline and at the end of the study, providers in both arms will be asked to complete a survey (See Appendix 5). The survey will assess provider role/department, level of experience, knowledge and motivation regarding current CC screen and treat guidelines, and barriers and facilitators to provision of complete CC screening services. End of study surveys will also include level of direct engagement with CATSystem and adapted quantitative items from the Acceptability of Intervention Measure (AIM), Intervention Appropriateness Measure (IAM), and Feasibility of Intervention Measure (FIM) four-item measures of implementation outcomes that are often considered “leading indicators” of implementation success. Providers will be eligible to complete the survey if they (1) work primarily in CCC, laboratory, or MCH/FP departments, (2) will/have been involved in the provision of CC screening and treatment during the course of the study, and (3) have interacted with the CATSystem during the course of the study (intervention sites only). We estimate n=5 providers per site for a total of n=50 provider surveys (n=25 intervention, n=25 control). Providers will complete informed consent prior to surveys.

**Supportive Supervision Visits** will occur monthly at all sites. Site Coordinators will provide technical assistance and retraining, review study materials (informed consent forms, surveys), and review data for completeness and accuracy. The monthly frequency of site visits has been adequate in previous HITSystem studies.

Aim 2 methods will include surveys and focus groups with CATSystem users, described below:

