**Surveys & focus groups with providers:** We will conduct semi-annual surveys (yrs 2 and 3) and FGD at each intervention site with all providers who routinely participate in CC screen and treatment services, including providers in the MCH/FP and CCC departments and laboratory staff (Appendix 6). We expect 5-8 providers with diverse levels of skill, years of experience and levels of knowledge involved in CC services at each site will participate in FGDs. The FGDs at intervention sites will be guided by TDF domains to understand *how* to best achieve the targeted CATSystem outcomes given the patient flow in their department and system-level challenges for the specific type of care they deliver. We will also monitor and elicit provider feedback on system and implementation modifications to better complement hospital workflow. *To ensure we are responsive to providers we will conduct FGD check in's twice a year in years 2 and 3 (see Appendix).*

**FGDs with women enrolled in CATSystem:** In year 3, two surveys and FGDs will be conducted at each intervention site: a) one with women enrolled in the CATSystem who received a positive screen and received appropriate treatment, and b) one with women enrolled in the CATSystem who received a positive screen and did not receive appropriate treatment. We expect 5-8 women in each of 2 FGDs per site (50-80 women total). Women who disengaged from CC care for >6 months but re-engaged after being prompted by Aim 2 engagement will still be counted as loss to follow-up for Aim 1 analyses. Similar to provider FGDs

we will use TDF domains to understand how participants experienced CC care, their experience with CATSystem, and factors that motivated them to complete treatment or describe barriers to treatment, see Appendix 7.

Procedures: Providers and participants who agree to participate will sign an informed consent specific to survey and FGD participation, respectively. FGDs will be conducted in a conference room at the facility, in the language the group feels most comfortable with (English, Kiswahili or both) and will be audio-recorded for later transcription and translation. FGDs will last approximately 30-45 minutes, allowing opportunity to learn from each other's experiences interacting with the CATSystem and identify opportunities to optimize the system.

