### **C. Sample size, statistical methods, and power calculation**

**Outcomes. The primary outcome of SA 1** will be receipt of appropriate treatment (onsite or referral, as indicated) for clients with a positive screen. Figure 5 illustrates treatment scenarios for women with a positive screen and the targeted timeframe for treatment. Women with coinfections (cervicitis/STI) must receive treatment, resolution, and rescreening within 3 months to determine infection status and appropriate action. Patients with a positive screen for precancerous lesions should ideally receive same day onsite treatment with cryotherapy (max duration of 5 days/1 wk) or referral (in/outside facility) to LEEP for advanced lesions (w/in 5 days/1 wk) with treatment follow-up and negative rescreen. If suspected of invasive CC, a referral to KNH or MTRH for chemo/ radiotherapy within the month.

We will identify women presenting with precancerous lesions (mild, moderate or severe), suspicious of invasive CC, or those with unreliable screen results due to cervicitis/STI or other comorbidity in each arm. We will then determine if guideline adherent treatment was provided based on severity of screening results. Retention time from first screening to last follow-up will also be calculated and compared by arm. Patient and facility-level factors, including aggregated provider characteristics, will be assessed for their moderating impact on receipt of appropriate treatment after a positive screen. To assess pathways through which the CATSystem works, we will measure provider and patient information, knowledge and motivation as potential mediators pre- and post-intervention across arms.

Secondary Outcome: We will determine whether each participant is screened for CC during the intervention period and use these data to assess the effect of the CATSystem intervention on odds of screening. To adjust for sites' pre-intervention screening rates, we will compute the proportion of women screened for CC cancer during the pre-intervention period and include this variable as a covariate in modeling.

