**Statistical analyses for SA1 primary outcome.** To demonstrate the efficacy of CATSystem verses SOC to increase the odds of women with a positive screen receiving treatment, we will model odds of treatment as a function of study arm and selected covariates (e.g., age, partner support, HIV status) using a logistic mixed model with a random site intercept included to adjust for clustering. Between-within degrees of freedom specified to adjust for downward bias in standard error estimates when the number of clusters is not large. Matching of sites prior to randomization will improve balance between arms on site-level

characteristics. Inclusion of covariates in the model will provide additional control for between-arm differences. We will use propensity score weighting to adjust for any severe, unanticipated imbalance between arms.

In post hoc analyses we will explore baseline patient and facility-level characteristics as potential correlates and moderators of the effect of CATSystem. Effects of these characteristics will be assessed by adding main effect and study arm×characteristic interaction terms to the logistic mixed model described above. We will also examine changes from baseline for key individual level factors [HIV status, partner support (see patient baseline survey in appendix)] for the two study arms. In further analyses, we will examine provider [level of experience, knowledge and motivation (see Provider survey in appendix)] as a mediator of the intervention's effect on odds of receiving treatment by fitting two models for each domain score: (1) A generalized or linear mixed model with change in knowledge from baseline to end of study as outcome and study arm as explanatory variable, and (2) a log-binomial mixed model with receipt of treatment as (binary) outcome and change in provider knowledge from baseline to end of study as explanatory variable. Estimates from these models will be combined to assess direct and indirect effects of the intervention. We will similarly assess provider motivation, participant knowledge, and participant motivation as potential mediators.

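### The exploratory mediation analysis uses provider and patient scores that need not precede treatment, so its indirect effects cannot be told apart from reverse causation

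*Protocol*

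**What the plan says.** Section II.C (Outcomes, repeated in V.B) wants to learn how the CATSystem works and states that "we will measure provider and patient information, knowledge and motivation as potential mediators pre- and post-intervention across arms".

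The analysis text in II.C (repeated in V.A) sets out two models per domain score. The first takes change in "knowledge from baseline to end of study as outcome and study arm as explanatory variable". The second is a log-binomial mixed model with "receipt of treatment as (binary) outcome and change in provider knowledge from baseline to end of study as explanatory variable". Then: "Estimates from these models will be combined to assess direct and indirect effects of the intervention". The same method is extended to three more scores: "We will similarly assess provider motivation, participant knowledge, and participant motivation as potential mediators".

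The measurement times are fixed under Procedures in II.B:

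- Providers, both arms: "At baseline and at the end of the study, providers in both arms will be asked to complete a survey".
- Providers, intervention arm only, for Aim 2: "We will conduct semi-annual surveys (yrs 2 and 3) and FGD at each intervention site".
- Patients: an enrolment survey, then for women positive for precancerous lesions a second survey with the same measures, "within 6 months of the positive screen or at the conclusion of treatment (both arms, Appendix 2").

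No sentence requires a mediator to be measured before the woman's treatment outcome.

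**The concern.** An indirect effect is a causal quantity: the arm changes the mediator, and the mediator then changes the outcome. The mediator must therefore come before the outcome. Here the provider score that completes the change is taken when the study ends, and the second patient score may be taken because treatment has finished.

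The arrow can then run backwards. Being counselled and treated can raise a woman's knowledge and motivation, and delivering treatment over the study can raise a provider's. If the CATSystem increases treatment by any route, a score with no causal role acquires some arm difference and some association with treatment. The two-model method would count the product of these as an indirect effect. Adding study arm to the outcome model does not restore the time order. What is at stake is the conclusion about pathways.

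**Working it through.** **1. Time order, from the protocol's own schedule**

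| Item | When | Section |
|---|---|---|
| Treatment of precancerous lesions | ideally same day, at most 5 days/1 week (LEEP referral likewise) | II.C |
| Referral for suspected invasive cancer | within the month | II.C |
| Coinfection treated, resolved, rescreened | within 3 months | II.C |
| Enrolment | spread over 24 months | II.C |
| Second provider score, both arms | end of study | II.B |
| Second patient score | within 6 months of the positive screen, or at the end of treatment | II.B |

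The end-of-study provider score follows nearly every outcome it is used to explain. The semi-annual provider surveys cannot supply an earlier score in both arms, because they are done at intervention sites only. For patients, the 6-month limit is longer than each dated window above, and the alternative timing is triggered by completing treatment. Some women may be surveyed before any treatment, but nothing requires it.

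**2. Inputs for an illustration**

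The protocol gives no figure for the mediation analysis. The sample-size text in II.C supplies treatment rates of 0.10 (SOC) and 0.35 (CATSystem) and five clusters of 30 per arm, so 150 women per arm. As a check on these inputs, the protocol's closed-form power reproduces:

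- Design effect = 1 + (30 − 1) × 0.05 = 2.45.
- Variance = (0.10 × 0.90 + 0.35 × 0.65) × 2.45 / 150 = 0.00519, so SE = 0.072.
- Noncentrality = 0.25 / 0.072 = 3.47. With a t reference on 8 df and 1-sided 0.025, power is 85.9%, as stated.

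The illustration sets the true effect of knowledge on treatment to zero and lets treatment raise a woman's later knowledge score by d SD. The values of d are assumptions. Clustering is ignored.

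**3. Arm path (arm to knowledge change)**

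Expected arm difference = d × (0.35 − 0.10). For d = 0.3 this is 0.075 SD, and for d = 0.5 it is 0.125 SD. The SE is about √(1/150 + 1/150) = 0.115, giving z of about 0.65 and 1.08. At 2-sided 0.05 the chance of significance is then roughly 10% and 19%. Simulation gave 9% and 21%.

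**4. Simulated results, arm included in the outcome model**

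| Quantity | d = 0.3 | d = 0.5 |
|---|---|---|
| Knowledge-treatment path, p<0.05, logistic | 51% | 90.5% |
| Same path, log link, two separate runs | 53%, 54% | 92%, 93% |
| Both paths p<0.05, the same two log-link runs | 4%, 6% | 19%, 18% |
| Spurious indirect risk ratio, the same two runs | 1.014, about 1.02 | 1.045, about 1.04 |

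Testing the arm path at site level with 8 df gives both paths in 4% and 15%.

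A further set of 400 data sets counted only positive associations at 2-sided p<0.05, so the nominal rate is 2.5%. With the outcome model as written (no arm term), the knowledge-treatment path was positive in 2%, 31%, 95% and 100% for d = 0, 0.2, 0.5 and 0.8. With arm added it was 3%, 27%, 92% and 100%. Without the arm term, the spurious indirect risk ratio was 1.00, 1.01, 1.05 and 1.12.

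**5. Size against the total effect**

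The total risk ratio is 0.35 / 0.10 = 3.5, with log 1.253. The spurious share is ln(1.014) / 1.253 = 1.1% at d = 0.3 and ln(1.045) / 1.253 = 3.5% at d = 0.5.

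**The case against.** Several points against the concern carry weight.

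- **The combined effect is small.** A reader might infer from the 50% to 93% that a false indirect effect will usually be reported. The documents and the calculation do not support this. That figure concerns one path only, whereas the plan combines two. The protocol also says it will judge results on effect sizes and confidence intervals and not on a 0.05 threshold. This stands. It limits the size of the problem, but the estimate remains biased whichever way it is summarised.
- **The illustration concerns patients, while the quoted model concerns providers.** Providers are not treated; they number about 5 per site, and their reverse path is experience gained by delivering care. This stands: no figure is available for the provider bias.
- **Measured late is not the same as occurring late.** Training takes place at all sites before launch, so provider knowledge may change early and the final score may be a late proxy. This is possible. It makes it too strong to infer that the pathway aim can never be informed by these data, but nothing in the schedule can show that the change came early.
- **The patient survey has two timings.** A reader might infer that it always follows treatment, or that each timing belongs to treated or untreated women. The protocol says neither. The defect is that it may follow treatment, and that its timing may depend on treatment.
- **The analysis is exploratory, and detail may sit in an SAP.** It is indeed exploratory. But survey timing is fixed in the protocol, and no SAP can recover a mid-study control-arm provider score that was never collected.

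**Conclusion.** The point holds in a limited form. The mediators are measured after the treatment outcome (providers) or are not required to be measured before it (patients). The plan nevertheless labels the combined estimates direct and indirect effects, and it cannot separate mediation from reverse causation.

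For the patient mediator, with no true mediation and an assumed d of 0.3 to 0.5 SD, the knowledge-treatment path is significant in about 50% to 93% of data sets. Both paths are significant in about 4% to 19%, and the spurious indirect risk ratio is about 1.01 to 1.05. These figures rest on the protocol's assumed treatment rates, on the assumed d and on ignoring clustering. The provider bias has a clear mechanism but no estimated size.

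A reader might infer that the trial's efficacy result is compromised. It is not: neither the primary treatment model nor the secondary screening model uses these scores.

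**What to change.** **1. Wording change in II.C and V.A.** Report the patient follow-up knowledge and motivation scores as post-treatment outcomes by arm. Use the enrolment scores only as moderators or covariates. Report the relation between provider change and treatment as an association, without direct and indirect effects. The cost is protocol wording and the loss of the participant-level mediation claim, which II.C lists among its aims.

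**2. Optional, if a provider mediation claim is to be kept.** Add the knowledge and motivation items for providers in both arms at the mid-point, when the facility assessment form is already completed at all sites. Relate baseline-to-midpoint change to women who screen positive afterwards. This means about 50 extra short surveys (5 providers at each of 10 sites).

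The second option has two drawbacks. It leaves about half of the positive women or fewer, since the protocol expects monthly enrolment may fall. At best that is 30 / 2 = 15 per site, of whom about 15 × 0.10 = 1.5 (SOC) or 15 × 0.35 = 5 (CATSystem) would be treated. And the mid-point change can still reflect treatment delivered in the first half, so site-level reverse causation is reduced but not removed.

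### The mediation outcome model is written without study arm, so as worded it gives no direct effect and can credit an inert mediator with part of the arm effect

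*Protocol*

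**What the plan says.** Protocol II.C, under the statistical analyses for the SA1 primary outcome, describes a mediation analysis. Provider characteristics are examined "as a mediator of the intervention's effect on odds of receiving treatment" by fitting two models per domain score. Model (1), a generalized or linear mixed model, takes change in "knowledge from baseline to end of study as outcome and study arm as explanatory variable". Model (2), a log-binomial mixed model, has "receipt of treatment as (binary) outcome and change in provider knowledge from baseline to end of study as explanatory variable". The next sentence states the purpose: "Estimates from these models will be combined to assess direct and indirect effects of the intervention". The scheme is then extended: "We will similarly assess provider motivation, participant knowledge, and participant motivation as potential mediators". Section V.A repeats this text.

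Arm is named as the predictor in model (1) and not named in model (2). Nothing elsewhere in the protocol adds it.

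Participant knowledge and motivation are measured at enrollment and, for women who screen positive, again "within 6 months of the positive screen or at the conclusion of treatment" (II.B, Participant surveys).

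**The concern.** A direct effect is the effect of arm with the mediator held fixed. To estimate it, arm and mediator must stand together in one outcome model. Neither written model has both.

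The indirect effect is affected too. The intervention is expected to act through alerts, SMS and tracing as well as through knowledge and motivation. If arm also moves the mediator, the two are correlated, and a model holding only the mediator lets its slope absorb what arm does by the other routes. Multiplying that slope by the arm effect from model (1) then overstates mediation and can produce it from nothing. The protocol says it wants to learn the pathways through which the CATSystem works, and that is the conclusion at risk.

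Subtracting the product from the total effect in the primary model is no remedy. A biased indirect effect leaves a biased remainder, and the primary model is on the odds scale while model (2) is on the risk-ratio scale.

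**Working it through.** **Inputs from the protocol (II.B, II.C).** Treatment rates 0.10 (SOC) and 0.35 (CATS), so the risk ratio is 3.5 and its log is 1.253; five clusters of 30 per arm; about 5 surveyed providers per site. **Assumed, not in the protocol:** the shift d of the mediator between arms, in SD units, and a site intercept SD of 0.45 on the logit scale.

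**1. The plan's own figure.** The mediation analysis has none. The primary power check does reproduce: design effect 1 + 29 × 0.05 = 2.45; standard error √[(0.10 × 0.90 + 0.35 × 0.65) × 2.45 / 150] = 0.0720; 0.25 / 0.0720 = 3.47; noncentral t on 8 df, one-sided 0.025, gives 85.9%, as stated. This figure is not in dispute.

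**2. Algebra for an inert mediator.** Let arm A be balanced (variance 0.25), M = d·A + noise with SD 1, and let log risk depend only on A, with coefficient θ. With A left out, the linear-approximation slope on M is θ × 0.25d / (1 + 0.25d²). Multiplied by the model (1) effect d, the apparent indirect effect is θ × d² / (4 + d²). The true value is 0.

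**3. Large-sample check.** 400,000 records, M with no effect on treatment, log-link Poisson fit, no random site intercept:

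| d (assumed) | risk ratio per SD of M | product | share of log 3.5 | d²/(4+d²) |
|---|---|---|---|---|
| 0 | 1.00 | 0.00 | 0% | 0% |
| 0.2 | 1.06 | 0.01 | 1% | 1% |
| 0.5 | 1.14 | 0.07 | 5% | 6% |
| 0.8 | 1.21 | 0.15 | 12% | 14% |
| 1.0 | 1.26 | 0.23 | 18% | 20% |
| 1.5 | 1.31 | 0.40 | 32% | 36% |

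With arm added, the mediator's log risk ratio is between −0.001 and 0.006 and the arm coefficient returns a risk ratio of about 3.5.

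**4. Effect of a random site intercept.** Model (2) is called a mixed model. A random site intercept takes up part of the between-arm difference, so for a participant mediator the bias is smaller than in step 3. A check at trial size (10 sites of 30, 150 runs, log-link with random site intercept, no arm) gave shares of about 1%, 6% and 16% at d = 0.5, 1.0 and 1.5. With arm added the slope was about 0.

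**5. Provider mediators.** If provider scores are averaged within site, the mediator is constant within site and the random intercept gives no such protection. The mean of 5 providers has SD 1/√5 if sites do not otherwise differ, so d provider SDs is d√5 site-level SDs, and the formula becomes 5d²/(4 + 5d²): 24%, 44% and 56% at d = 0.5, 0.8 and 1.0. Trial-size simulation (800 runs, regression of site log rates) gave products of 0.38, 0.63 and 0.75, or 30%, 50% and 60% of 1.253. Part of that is chance difference between ten site means: at d = 0 the product still averaged 0.127, about 10%.

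**6. How often an inert mediator is nominally significant** (trial size, 800 runs; the participant-level fit used cluster-robust errors, which run somewhat high with ten clusters):

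| d | participant, no arm | participant, with arm | site, no arm | site, with arm |
|---|---|---|---|---|
| 0 | 7% | 8% | 4% | 4% |
| 0.5 | 25% | 7% | 20% | 5% |
| 0.8 | 51% | 10% | 40% | 6% |
| 1.0 | 60% | 10% | 50% | 6% |

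**The case against.** The strongest reply is that the sentence is a sketch. It never says the mediator is the only predictor, it lists no covariates for either model, and it cites a method paper on mediation with a dichotomous outcome. A separate SAP may name arm. This is a fair reason not to claim that the final analysis will be wrong. It does not remove the point: the text states the predictor of each model and names arm in one only, and the neighbouring moderator analysis names arm explicitly. An SAP that followed the protocol would carry the omission forward.

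Four stronger readings are tempting but not supported.

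- *Any mediator that differs by arm will look like a pathway.* This also requires that arm affect treatment by other routes. With no shift in the mediator there is no systematic bias.
- *A single headline share applies.* The shift d is not in the protocol, and the result differs between participant and site-level mediators and with the random intercept.
- *Participant mediators are always measured after the outcome.* The follow-up survey may fall within 6 months of the positive screen, and untreated women have no conclusion of treatment. Restricting the analysis to pre-treatment measurements would leave many women treated the same day with the enrollment survey only and no change score.
- *Model (1) compares engaged intervention providers with all control providers.* The third survey criterion, interaction with the CATSystem, does apply at intervention sites only. But the first two criteria restrict control providers as well, to relevant departments and to staff involved in screening and treatment. Relaxing the third would mean surveying more staff, not changing a line of analysis.

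**Conclusion.** The point holds in a limited form. As worded, model (2) supplies no direct effect, and its mediator slope mixes the mediator's effect with the arm's effect by other routes. Whether this produces false mediation depends on two conditions the trial anticipates but the protocol does not quantify: that the intervention shifts the mediator, and that it also works by other routes.

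For an individual-level mediator under the protocol's 10% and 35%, the spurious share runs from about 1% at 0.2 SD to 32% at 1.5 SD without a random intercept, and is lower with one. For provider mediators handled as site averages it may be larger, about 30% to 60% at 0.5 to 1.0 provider SD, under the assumptions shown.

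A reader might infer that the trial's main result is compromised. It is not: the mediation analysis comes under further analyses, after the post hoc ones, and the primary arm comparison, sample size and power do not depend on it. This is a mis-stated exploratory model, worth correcting because correction is cheap.

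**What to change.** In Protocol II.C and V.A, write model (2) with both study arm and the change in the mediator as explanatory variables. Keep the random site intercept, and include the primary-model covariates where the data allow. State that this applies to every listed mediator, and derive the direct and indirect effects from that model. State also the scale on which the effects are reported, since the target is worded as odds and model (2) is log-binomial.

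An arm-by-mediator interaction is optional. For a site-level mediator it means four fixed parameters on ten sites, with about 68 expected treated women (150 × 0.10 + 150 × 0.35 = 67.5).

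Describe participant-mediator results as associational where the follow-up survey was completed after treatment.

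The change is to wording and needs no new data. The price is wider intervals, because arm is constant within site and there are only ten sites.

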**Sample size considerations.** Assuming average success (treatment completion) rates of 0.10 (SOC arm) and 0.35 (CATS arm), we used R to simulate 5,000 data sets, each with outcome data for five 30-person clusters per arm. A target ICC value for each data set was randomly drawn from a half-normal distribution fit by Turner et al. (2001) to the empirical distribution of 70 ICCs from studies of health outcomes with data clustered within practices, towns, or postal codes. For simulation, each target ICC was converted to a random site intercept variance on the logistic scale using the assumed SOC success rate (0.10) and the Taylor expansion approximation from Turner et al. We simulated success counts for each cluster by drawing a random cluster intercept from a Gaussian distribution with the specified variance, adding the appropriate fixed intercept and (for CATS sites) arm effect on the logistic scale, converting the resulting logit to a probability (p), and taking a random Binomial(30, p) draw. This process reflects our uncertainty in the true ICC. It also produces ICCs larger than the target values because of bias in the Taylor approximation and our use of the SOC success rate to estimate the random intercept variance, which yields a larger ICC among CATS clusters due to their higher success rate. Thus, across the 5,000 data sets, mean ICC was 0.057 for SOC clusters and 0.083 for CATS clusters (vs. mean ICC 0.023 for the half-normal distribution fit by Turner et al.). For a point of comparison, analysis of pilot screening rate data for our ten study sites yielded ICC 0.012.

For each simulated data set we used SAS 9.4 to fit a logistic mixed model with a fixed arm effect and random site intercept. Between-within degrees of freedom were specified as a small-sample adjustment. The mean length of 95% CIs for the arm effect odds ratio was 18.0; power (1-sided test,  $\alpha=0.025$ ) was 86.9%. For comparison, the R package *clusterPower* (<https://CRAN.R-project.org/package=clusterPower>), which has been verified against NIH's GRT Sample Size Calculator and PASS11, yielded power=85.9% for the SOC and CATS rates and ICC=0.05.

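### The mean simulated ICCs of 0.057 and 0.083 appear to include binomial sampling noise; the 86.9% power applies at about 0.026 (SOC) and 0.051 (CATS)

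*Protocol*

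**What the plan says.** All of this is in the protocol, section II.C, under the sample size considerations.

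- Rates and design: "Assuming average success (treatment completion) rates of 0.10 (SOC arm) and 0.35 (CATS arm"), with R used to "simulate 5,000 data sets, each with outcome data for five 30-person clusters per arm".
- Clustering: each data set's target ICC is drawn from a half-normal distribution and "converted to a random site intercept variance on the logistic scale using the assumed SOC success rate (0.10) and the Taylor expansion approximation". The same variance serves both arms. Counts are then generated by "converting the resulting logit to a probability (p), and taking a random Binomial(30, p) draw".
- Result: "across the 5,000 data sets, mean ICC was 0.057 for SOC clusters and 0.083 for CATS clusters". The target distribution itself has a mean of 0.023.
- Reason given for the excess: "It also produces ICCs larger than the target values because of bias in the Taylor approximation", together with use of the SOC rate to set the intercept variance, which raises the ICC in the CATS arm.
- Power: 86.9% (one-sided test, alpha 0.025) from a logistic mixed model with between-within degrees of freedom. As a comparison, clusterPower "yielded power=85.9% for the SOC and CATS rates and ICC=0.05".

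The section also gives a pilot ICC of 0.012, for screening rates. It does not say how the ICC of a simulated data set was calculated, and it does not print the Taylor formula.

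**The concern.** The step from a target mean of 0.023 to 0.057 in the SOC arm is too large for the cause given. The conversion to an intercept variance is made at the SOC rate, so only the error of the approximation can move the SOC value, and that error should be small at these ICCs.

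The two power figures also sit awkwardly together. Power of 85.9% at a uniform ICC of 0.05 is hard to square with 86.9% at 0.057 and 0.083, where clustering is stronger in both arms.

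What is at stake is the stated margin against clustering. Set beside the pilot 0.012, the printed values suggest that power holds at about five to seven times that ICC (0.057/0.012 = 4.8; 0.083/0.012 = 6.9). With ten clusters, and no ICC given for treatment completion itself, a reader will lean on that margin.

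**Working it through.** **Inputs, all from section II.C.** Success rates 0.10 and 0.35; 5 clusters of 30 per arm; target ICC half-normal with mean 0.023 (scale 0.023 × sqrt(pi/2) = 0.0288); conversion at p = 0.10; Binomial(30, p) counts; one-sided alpha 0.025. Two inputs are assumptions. The Taylor conversion is taken as intercept variance = ICC/(0.10 × 0.90), with ICC/[(1-ICC) × 0.09] as a variant. The between-within degrees of freedom are taken as 10 - 2 = 8.

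**1. The plan's own power figures.** Closed form, noncentral t with 8 df:

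ncp = 0.25 / sqrt{[0.09(1 + 29 ICC_SOC) + 0.2275(1 + 29 ICC_CATS)] / 150}

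At ICC 0.05 in both arms: 0.09 × 2.45 = 0.2205; 0.2275 × 2.45 = 0.5574; SE = sqrt(0.7779/150) = 0.0720; ncp = 3.47; power 85.9%, which matches the plan.

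The described simulation (3,000 data sets), fitted by residual pseudo-likelihood with 8 df, gives 87.1% against the stated 86.9%. Maximum likelihood by quadrature gives 91.1%. The 86.9% is therefore reproduced for the process simulated.

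**2. The ICCs of that process.** True ICC here means the variance of the cluster probabilities over p(1-p), averaged over the half-normal draws. The estimators were applied to 200,000 simulated data sets.

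| Quantity | SOC | CATS |
|---|---|---|
| True ICC | 0.026 | 0.051 |
| Range over conversion variants | 0.024-0.027 | 0.050-0.053 |
| ANOVA estimate, mean | 0.023 | 0.050 |
| ANOVA truncated at zero, mean | 0.028 | 0.053 |
| Observed-proportion variance / [pbar(1-pbar)] | 0.056 | 0.084 |
| Printed in the protocol | 0.057 | 0.083 |

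Only the uncorrected ratio comes close to the printed pair. The variance of an observed proportion from 30 women contains binomial variance, which adds (1-ICC)/30 to the ratio:

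- SOC: 0.026 + 0.974/30 = 0.026 + 0.032 = 0.058
- CATS: 0.051 + 0.949/30 = 0.051 + 0.032 = 0.083

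**3. Can both printed values be true ICCs?** Each data set has one intercept variance for both arms.

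- A variance of 0.541 gives a true SOC ICC of 0.057, but then CATS is about 0.103.
- A variance of 0.421 gives a true CATS ICC of 0.083, but then SOC is about 0.043.

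Averaging over the half-normal does not remove the conflict. The distribution would have to be scaled up by 2.14 to bring the SOC mean to 0.057, but by 1.81 to bring the CATS mean to 0.083.

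**4. Power by level of clustering (closed form of step 1).**

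| ICC SOC / CATS | SE | ncp | Power |
|---|---|---|---|
| 0.026 / 0.051 | 0.0694 | 3.60 | 88.3% |
| 0.050 / 0.050 | 0.0720 | 3.47 | 85.9% |
| 0.057 / 0.083 | 0.0822 | 3.04 | 75.9% |

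Simulating with separate intercept variances, so that the true ICCs are 0.057 and 0.083, gives 72.2% by pseudo-likelihood and 79.5% by quadrature. The 86.9% therefore belongs with the lower pair.

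**The case against.** **The estimator is not printed.** Nor is the Taylor form. This stands: the source of the printed pair is inferred. The inference is strong, because it matches both arms and the pair fails the common-variance check, but only the sponsor's code can settle it.

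**The explanation is right in direction.** This also stands. Taylor bias does raise the SOC value, from 0.023 to about 0.026. Use of the SOC rate does raise the CATS value to about 0.051, nearly half of its printed excess: (0.051 - 0.023)/(0.083 - 0.023) = 0.47. The explanation accounts for too little, so it should be amended rather than removed.

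**The comparison run is sound.** It states its own ICC of 0.05, and 85.9% is correct there. A reader might infer that it was meant to confirm power at the printed means and fails to do so. The protocol offers it only as a comparison.

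**No design element changes.** True: sample size, outcome, model and alpha all stay. A reader might infer that the trial's real power is 76%, or that it is underpowered. The documents do not support that. The 75.9% is conditional on ICCs that the simulation did not reach and that the protocol does not predict for this outcome. Nor is a miss rate of 24% or more supported: with power of about 72-80% at the printed pair, the miss rate is about 20-28%. Power of 68%, which a run with intercept variance of about 0.54 in both arms gives, corresponds to about 0.057/0.103 and is harsher than anything the protocol states.

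**Conclusion.** The concern holds as a misstated design figure. The printed mean ICCs exceed the clustering actually simulated by about 0.03 in each arm, and the reason given explains only part of the gap. The 86.9% is correct for the simulated process, but it applies at about 0.026 (SOC) and 0.051 (CATS). If the ICCs were as high as 0.057 and 0.083, power would be about 76% by the closed form, or about 72-80% depending on the fitting method.

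Relative to the pilot screening ICC, the clustering tested is about two to four times as large (0.026/0.012 = 2.2; 0.051/0.012 = 4.3), not five to seven.

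This rests on the assumed Taylor conversion (both variants tried agree), 8 degrees of freedom, and the inferred estimator. That the printed pair cannot both be true ICCs does not depend on the inferred estimator or on the assumed Taylor form, only on the single intercept variance that the protocol describes.

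**What to change.** In the sample size considerations of section II.C:

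1. State how the ICC of a simulated data set is calculated. Recompute the means net of binomial sampling variance from the sponsor's own code, and replace 0.057 and 0.083 with the results (expected about 0.026 and 0.051).
2. Amend the explanation: Taylor bias adds only a little in the SOC arm (0.023 to about 0.026), and use of the SOC rate accounts for the larger CATS value.
3. State that the 86.9% applies at the recomputed ICCs.
4. Add that power would be about 76% by the closed form (about 72-80% by fitting method) if the ICCs were 0.057 and 0.083, and name the fitting method used in SAS. If that sensitivity figure is simulated, say that this pair needs a different intercept variance in each arm.

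The cost is a re-run of existing code and a few sentences. Sample size is unchanged. The downside is that the plan will show less robustness to clustering than it now appears to.
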